## Abstract

**Background:**

Contrast-induced nephropathy (CIN) is a serious clinical problem associated with increased morbidity and mortality, particularly in patients with chronic renal insufficiency. Although some agents including hydration with saline are being prescribed to prevent renal deterioration in these high risk patients, their efficacy is not clearly defined and debatable. Therefore additional prophylactic pretreatments are needed.

**Methods/Design:**

The present study aims to investigate differences in occurrence of CIN after sarpogrelate premedication in patients with chronic kidney disease (CKD). 268 participants, aged 20-85 years with a clinical diagnosis of CKD will be recruited. They will be randomly allocated to one of two conditions: (i) routine treatment without sarpogrelate, and (ii) routine treatment with sarpogrelate (a fixed-flexible dose of 300 mg/day). The primary outcome is the occurrence of CIN during 4 weeks after receiving contrast agent.

**Discussion:**

As of May 2010, there were no registered trials evaluating the therapeutic potentials of sarpogrelate in preventing for CIN. If sarpogrelate decreases the worsening of renal function and occurrence of CIN, it will provide a safe, easy and inexpensive treatment option.

**Trial registration:**

NCT01165567

## Background

Contrast-induced nephropathy (CIN) is a common form of hospital-acquired acute renal failure (ARF) after coronary angiography (CAG) and percutaneous coronary intervention (PCI) and is associated with prolonged hospitalization and adverse clinical outcomes [1,2]. Patients undergoing PCI have a higher mortality rate if the nephropathy develops [3]. Although its incidence is low in patients with normal renal function, it can be much higher in those with renal insufficiency at baseline [4,5]. Adequate prophylaxis is needed to reduce the higher morbidity and mortality associated with CIN in high-risk patients. A variety of therapeutic interventions, including saline hydration, diuretics, mannitol, calcium channel antagonists, theophylline, endothelin receptor antagonists, and dopamine, have been used in an attempt to prevent CIN [6-9]. Hydration with normal saline solution is the most widely accepted preventive intervention [9,10]. But the nephropathy occurred in 20~30% who received the recommend treatment [11,12], it means current treatments are not enough and the optimal strategy to prevent CIN has not been established.

Although the pathogenesis of this condition is not fully understood, it is most likely the result of renal ischemia and direct toxicity to tubular epithelial cells [13,14]. After contrast is injected, renal blood flow transiently increases and then decreases over a longer time, suggesting that renal ischemia is a major factor in the pathogenesis of CIN [13]. Contrast agents reduce the oxygen tension in both the cortex and the medulla [14]. Many studies suggest that contrast agents are directly toxic to kidney cells, causing proximal cell vacuolization, interstitial inflammation, cellular necrosis, and enzymuria [15].

Sarpogrelate is a selective 5-hydroxytryptamine receptor subtype 2A (5-HT_2A_) antagonist that inhibits responses to 5-HT mediated by 5-HT_2A _receptors such as platelet aggregation, vasoconstriction, and vascular smooth muscle proliferation [16-18]. Its chemical structure is illustrated in Figure 1. Several studies demonstrated that sarpogrelate is efficacious treatment in thrombosis, coronary artery spasm, atherosclerosis, restenosis, peripheral artery disease, diabetes and kidney disease [16,17,19-23]. Especially small clinical trial had shown that sarpogrelate has a renal protective potential [23,24]. A pilot study demonstrated that sarpogrelate improved the symptoms and signs of diabetic nephropathy and neuropathy in three of eight patients with Type 2 diabetes and mild nephropathy [25]. Sarpogrelate also reduced the urinary and plasma levels of thromboxane A_2 _and this may be associated with the reduced albumin excretion [26]. Another study demonstrated that sarpogrelate reduced albuminuria in diabetic patients with early-stage diabetic nephropathy within 3 months [27]. Therefore, we might hypothesize that sarpogrelate would have shown positive results in prophylaxis of CIN.

**Figure 1 F1:**
[figure not shown]
**Structure of sarpogrelate**.

The primary hypothesis to be tested is whether sarpogrelate significantly reduce the occurrence of CIN during 4 weeks follow-up period, compared with the control group.

## Methods/Design

The study is designed as a non-blinded, prospective, randomized controlled clinical trial to evaluate efficacy and safety of sarpogrelate in CKD patients undergoing CAG and PCI. After a baseline measurement, participants were randomly allocated into the treatment group (routine treatment with sarpogrelate) or the control group (routine treatment without sarpogrelate). In this study, routine treatment is defined as saline hydration and benefit of sarpogrelate is assessed as an adjunct to saline hydration for the prevention of CIN following diagnostic CAG or PCI

Study approval was given by the Ethics Committee/Institutional Review Board of Seoul National University Boramae Medical Center.

### Participants

All patients with CKD scheduled for CAG will be eligible, assuming their ability to understand the character and individual consequences of participation as well as giving written informed consent. CKD is defined as estimated glomerular filtration rate (eGFR) <60 mL/min per 1.73 m^2 ^using modification of diet in renal disease (MDRD) formula or serum creatinine (Cr) > 1.5 mg/dL.

The MDRD formula was defined in the following way. Where the Cr concentration is in mg/dL:

$$\text{eGFR}=\text{186}\times {\text{serum Cr}}^{-1.154}\times {\text{Age}}^{-0.203}\times \left(0.\text{742 if female}\right)$$

Exclusion criteria are age less than 20 years or more than 85 years, liver cirrhosis greater than or equal to Child class B, decreased serum platelet level (< 100,000/uL), patients who received or are schedule to receive percutaneous renal intervention, currently are taking anticoagulation drugs, unable to give informed consent. Patients in shock, maintaining hemodialysis, hemofiltration, peritoneal dialysis will be excluded.

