### Primary Outcome Measurement

The primary outcome of the study is the incidence of CIN, defined as either a greater than 25 percent increase of serum Cr or an absolute increase in serum Cr of 0.5 mg/dL within 48 hours after using contrast agent [28,29]. Clinical endpoint measurements are conducted in-hospital and at 4 weeks. Cr concentration is measured at admission, every day for the next two days after contrast exposure, and at 4 weeks.

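### The CKD entry rule has no stability, acute renal failure or recent-contrast condition, so the criteria permit patients whose creatinine is already moving to be scored as CIN or to hide it

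*Protocol article*

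**What the plan says.** **Entry.** The Participants section of the protocol article opens with "All patients with CKD scheduled for CAG will be eligible". The operative definition follows: "CKD is defined as estimated glomerular filtration rate (eGFR) <60 mL/min per 1.73" m² by the MDRD formula, "or serum creatinine (Cr) > 1.5 mg/dL". Either limb is enough. No duration, repeat value or stability requirement is attached. The Abstract (Methods/Design) describes participants as clinically diagnosed with CKD and does not say how that diagnosis is established.

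**Exclusions.** The list in the same section covers age, cirrhosis, low platelets, percutaneous renal intervention, anticoagulant use and inability to consent. The entry nearest to acute renal failure is "Patients in shock, maintaining hemodialysis, hemofiltration, peritoneal dialysis will be excluded". Acute renal failure without dialysis, a creatinine that is rising or falling at admission, and contrast received shortly beforehand are not named.

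**Outcome.** Under Primary Outcome Measurement, CIN is a "greater than 25 percent increase of serum Cr or an absolute increase in serum Cr of 0.5 mg/dL within 48 hours" of contrast. On sampling, "Cr concentration is measured at admission, every day for the next two days after contrast exposure, and at 4 weeks". That is one scheduled pre-contrast value. No step separates contrast from other causes of a rise.

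**The concern.** The trial's aim is to prevent contrast injury in patients with chronic renal impairment. The entry rule and the outcome both work on the level of creatinine, and neither asks whether that level was steady before contrast.

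Two things can go wrong. A patient whose creatinine is already climbing can cross the CIN threshold whatever the contrast or the drug does. A patient recovering from an earlier injury has a raised admission value, and a true contrast-related rise may then stay below the threshold. A single admission value cannot show either course.

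If such patients enter in any number, some primary events are ones that sarpogrelate could not have prevented, and some contrast events go uncounted. The treatment contrast is then harder to detect, and the CIN rate is harder to attribute to contrast.

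**Working it through.** **1. Do the criteria permit it?** Take a hypothetical patient with previously normal function whose creatinine has risen acutely to 1.6 mg/dL. Since 1.6 > 1.5, the creatinine limb is met, and no listed exclusion applies if there is no shock and no dialysis.
- *Rising course:* the patient scores CIN on passing 1.25 × 1.6 = 2.0 mg/dL, with or without a contrast effect.
- *Recovering course:* suppose creatinine would have fallen to 1.2 without contrast, and contrast adds 0.5. The measured value is 1.7, and 1.7/1.6 = 1.06, a 6% rise. No event is counted.

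**2. Planning figures (Sample size section).** Control rate 20%, a 50% difference (read as relative, so 10% on sarpogrelate), two-sided 5%, 80% power, 10% loss, 134 per group. The plan gives no figure for unstable patients, so the nearest figure to reproduce is the sample size:

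n = [1.96·√(2·0.15·0.85) + 0.842·√(0.20·0.80 + 0.10·0.90)]² / 0.10² ≈ 199 per group; 199/0.9 gives 222 after loss.

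The stated 134 is not reproduced. That is a separate matter, but it sets the starting power here. With 134 × 0.9 ≈ 120 evaluable per arm,

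power = Φ{[|p₁ − p₂|·√120 − 1.96·√(2p̄(1 − p̄))] / √(p₁(1 − p₁) + p₂(1 − p₂))} = 58% for 20% versus 10%.

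**3. Unrelated rises.** Assume a share b of patients in each arm has a rise from another process, on top of the planned rates: observed rate = b + (1 − b)·p. The documents give no value for b.

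| b (assumed) | Control | Sarpogrelate | RR | Difference | Power, 120 per arm |
|---|---|---|---|---|---|
| 0 | 20.0% | 10.0% | 0.50 | 10.0 points | 58% |
| 2% | 21.6% | 11.8% | 0.55 | 9.8 points | 53% |
| 5% | 24.0% | 14.5% | 0.60 | 9.5 points | 46% |
| 10% | 28.0% | 19.0% | 0.68 | 9.0 points | 38% |

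**4. Masking and mixtures.** Assume instead that a share f is unstable at entry and has event rate q in both arms: observed rate = (1 − f)·p + f·q.
- Pure masking (q = 0), f = 10%: 0.9 × 20% = 18% versus 0.9 × 10% = 9%. RR stays at 0.50; power with 120 per arm is 53%.
- f = 10%, q = 40%: 18% + 4% = 22% versus 9% + 4% = 13%. RR = 0.59; power is 45%.
- With 199 per arm, which gives 80% power at f = 0, the same two cases have 75% and 66%. The loss is therefore not only a product of the small stated N.

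**The case against.** **The Abstract mentions a clinical diagnosis of CKD.** The thresholds could be read as applying only to patients already known to have chronic disease. That is a fair reading and it narrows the gap. It does not close it: the Participants section says what CKD means for this trial, and that definition contains only the two thresholds.

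**The setting limits the opening.** Angiography is scheduled, shock and dialysis are excluded, and saline (with sarpogrelate in the treatment group) precedes contrast. This removes the most severe cases. It does not remove moderate acute injury, a recovering creatinine or contrast given earlier elsewhere.

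**An article condenses its protocol.** The full document might hold a stability rule. However, this article prints an operative definition and a specific exclusion list, so the criterion is stated rather than left out.

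**The 2–10% share has no source in the documents.** This stands; the share is purely an assumption. The cited 20% control rate may also already include rises from other causes, in which case adding b counts them twice. The effect then depends on what the 50% refers to. If it means half of all rises, 20% versus 10% holds and nothing is diluted relative to the plan. If it means half of the preventable rises, the treated rate is b + (0.20 − b)/2 = 11%, 12.5% and 15% for b = 2%, 5% and 10%, giving RR 0.55, 0.625 and 0.75.

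**Relative risk does not always move toward 1.** This also stands: masking alone leaves it unchanged and costs only events and power.

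**Randomisation balances these patients.** Allocation is 1:1 and concealed, so apart from chance imbalance no arm is favoured.

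**Conclusion.** The concern holds in a limited form. As written, the entry criteria permit patients with acute or recovering renal injury to enter, and the outcome definition can score their natural course as CIN or let it hide CIN. The expected result is dilution, lost power and weaker attribution to contrast.

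The size is unknown. Under the assumption of a 2–10% unrelated rise on top of 20% versus 10%, the observed RR is about 0.55–0.68 instead of 0.50, and power with about 120 per arm falls from 58% to 53–38%. Under pure masking the RR stays at 0.50, with fewer events and less power.

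Two stronger readings are tempting and not supported:
- *Acute renal failure does enter the trial, or enters often.* The text shows only that it is not excluded. Nothing in it gives a frequency, and even the reliance on a single value is inferred from the absence of a second-value requirement and the one scheduled pre-contrast measurement.
- *The result is biased toward sarpogrelate or toward control.* With concealed 1:1 allocation the documents give no ground for that.

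**What to change.** Amend the exclusions in the Participants section to add:

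1. Known acute renal failure, or a creatinine change meeting the trial's own CIN threshold (more than 25%, or 0.5 mg/dL) between admission and an earlier value inside a short look-back window that the sponsor fixes in advance. The window must be bounded; otherwise slow progression of CKD over a long interval would exclude the target population. Patients with no earlier value in the window stay eligible.
2. Iodinated contrast within a fixed number of days before randomisation, the number set by the sponsor.

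Recruitment began in April 2010. For patients already enrolled, apply the same rules as a flag, using pre-randomisation records only. The flagging should be done by a study member who sees neither allocation nor post-contrast creatinine, because the trial is open-label and informed flagging could select on outcome. Keep the intention-to-treat primary analysis as it is, and report the comparison without flagged patients as a sensitivity analysis. Since the flag rests on pre-randomisation data, that comparison remains a randomised one.

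The cost is a short amendment, a chart check of earlier creatinine values and contrast exposure, a few otherwise eligible patients lost and slightly slower recruitment. Unstable patients with no earlier value on record will still pass, so the fix reduces the problem without removing it.

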### Intervention

After a baseline measurement, all patients receive 0.9% saline or 0.45% saline intravenously at 150 ml/hour at least for 6 hours before and 6~8 hours after receiving contrast agent. Patients in the treatment group receive sarpogrelate 300 mg per day for 24 hours before exposure to contrast agent. Sarpogrelate will be given for 4 weeks.

Recruitment of participants started in April 2010. The process of the trial conduct is illustrated in Figure 2. No additional risks for study patients are expected, since all treatment is carried out within established standard methods of CAG or intervention.

**Figure 2 F2:**
[figure not shown]
**Study design**.

### Primary Outcome Measurement

The primary outcome of the study is the incidence of CIN, defined as either a greater than 25 percent increase of serum Cr or an absolute increase in serum Cr of 0.5 mg/dL within 48 hours after using contrast agent [28,29]. Clinical endpoint measurements are conducted in-hospital and at 4 weeks. Cr concentration is measured at admission, every day for the next two days after contrast exposure, and at 4 weeks.

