### Secondary Outcomes Measurement

Secondary outcomes are occurrence of CIN, performance of hemodialysis or hemofiltration and bleeding events at 4 weeks.

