### Statistical analysis

The statistical analyses are performed on an intention-to-treat basis. The two-sided null-hypothesis for the primary outcome measure states that sarpogrelate has the potential effect on preventing CIN in CKD patients undergoing CAG or PCI. Descriptive statistics will be calculated according to the scale level of the variables. The Kaplan- Meier method is used to plot the time to the first episode of CIN, performance of hemodialysis or hemofiltration and bleeding events after CAG or PCI.

Continuous data will be analyzed using Student's t-test. The chi-square test is used for categorical variables. A value of p < 0.05 is considered statistically significant. Efficacy analyses was performed on the full analysis set, which consist of patients who received at least 1 dose of study medication. Patients who take the medication at least once are analyzed for safety. Graphical methods including scatter plots and boxplots will be used to visualize the findings of the trial.

The safety analysis includes calculation of frequencies and rates of complications and serious adverse events reported in the two groups. All analyses will be done using SPSS Version 16.0 or higher.

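### The primary outcome is given two windows, 48 hours and 4 weeks, and CIN is listed again as an undefined secondary outcome, so the primary test is not fixed

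*Protocol article*

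**What the plan says.** Four places in the protocol article bear on the window.

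- **Abstract, Methods/Design:** "The primary outcome is the occurrence of CIN during 4 weeks after receiving contrast agent".
- **Background, closing statement of the primary hypothesis:** the question is "whether sarpogrelate significantly reduce the occurrence of CIN during 4 weeks follow-up period".
- **Primary Outcome Measurement:** CIN is a rise in serum creatinine of more than 25 percent, or "an absolute increase in serum Cr of 0.5 mg/dL within 48 hours after using contrast agent". The sampling schedule follows: "Cr concentration is measured at admission, every day for the next two days after contrast exposure, and at 4 weeks". No further creatinine sample is described.
- **Secondary Outcomes Measurement:** CIN appears here a second time, in a list that reads "Secondary outcomes are occurrence of CIN, performance of hemodialysis or hemofiltration and bleeding events at 4 weeks".

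The Statistical analysis section adds "The chi-square test is used for categorical variables" and "The Kaplan- Meier method is used to plot the time to the first episode of CIN". The Sample size section assumes a 20% CIN rate in the control group and names no window for it.

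**The concern.** The hypothesis and the outcome definition describe different events. A patient whose creatinine first crosses the threshold at the 4-week visit is a case under the Abstract and the hypothesis, but not under the outcome section. The secondary list uses the same term with no definition of its own, so primary and secondary CIN cannot be told apart.

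Two things are at stake. First, the trial is not blinded and both versions can be computed from samples already scheduled, so the choice of primary analysis could be made after the results are seen. Second, a 4-week version adds one late sample to the two post-contrast days. That sample also picks up creatinine changes that have nothing to do with contrast, and these would dilute the effect for which the trial is sized.

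**Working it through.** **1. Can the passages be reconciled?**

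| Reading | What it leaves unresolved |
|---|---|
| Four weeks is only the follow-up period; CIN is always the 48-hour event | The secondary list repeats the primary outcome, and the Abstract and hypothesis state the wrong window |
| In the secondary list, the 4-week phrase belongs to bleeding only | CIN is both primary and secondary with no distinction; the Abstract and hypothesis still conflict with the outcome section |
| The 48-hour limit belongs only to the 0.5 mg/dL criterion | The two criteria of one endpoint have different windows |

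None removes the conflict.

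**2. Inputs**

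- From the Sample size section: 20% in the control group; a 50% difference, read as relative (20% vs 10%); two-sided 5%; 80% power; 10% loss; 134 per group.
- Assumed, because the protocol gives no value: a proportion q of patients without CIN by 48 hours who show a late rise. It is taken as equal in both arms and unaffected by treatment.

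**3. The plan's own figure**

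The stated 134 does not follow from these inputs. The usual two-proportion formula gives 199 per group, and 199/0.9 = 221.1, so 222 after loss. That is a separate problem. It matters here only because the starting power is 63%, not 80%.

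Power = Φ[(d − 1.96·SE0)/SE1], where d is the difference in proportions, SE0 = √(2p̄(1−p̄)/n) and SE1 = √((p1(1−p1) + p2(1−p2))/n).

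For 20% vs 10% and n = 134: p̄ = 0.15, SE0 = 0.0436, SE1 = 0.0432. Then (0.1 − 0.0855)/0.0432 = 0.336, so power is 63%. With about 120 analysed per group it is 58%.

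**4. Type I error if either window may be claimed**

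Null simulation: 134 per arm, 20% CIN by 48 hours in both arms, and 4-week CIN counted cumulatively as the 48-hour events plus late rises. Each window is tested two-sided at 5% with a pooled two-proportion test.

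| q | Rejection on either window |
|---|---|
| 3% | 6.7% |
| 5% | 7.2% |
| 10% | 7.9% |

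These rates count both directions. By symmetry, false claims of benefit are half: 6.7/2 to 7.9/2, about 3.4–4.0%, against a nominal 2.5%.

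**5. Dilution if the 4-week window is primary**

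The rates become 1 − 0.8(1−q) in the control group and 1 − 0.9(1−q) in the sarpogrelate group.

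| q | Control | Sarpogrelate | Relative reduction | Power, n = 134 |
|---|---|---|---|---|
| 0 | 20.0% | 10.0% | 50% | 63% |
| 1% | 20.8% | 10.9% | 48% | 60% |
| 5% | 24.0% | 14.5% | 40% | 50% |
| 10% | 28.0% | 19.0% | 32% | 41% |

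**6. Why the control rate must be tied to a window**

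With a halved rate and 120 analysed per group, power is 31% at a 10% control rate, 45% at 15%, 58% at 20%, 70% at 25% and 80% at 30%. These rates are a range for illustration; the protocol gives none by window.

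**The case against.** The strongest defence is that CIN means the 48-hour event throughout and four weeks is simply how long patients are followed. The outcome section supports this, since it is the only place that gives CIN an operational definition. But 4 weeks is not clearly a slip: treatment lasts 4 weeks, creatinine is drawn then, and a time-to-first-CIN plot is planned. Nor is this detail that an article leaves to a fuller document, because the article itself states the window in two ways.

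Other objections stand and limit the point.

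- A reader might infer that CIN at 4 weeks is impossible under a 48-hour definition. The text does not support that: the secondary item can mean cumulative occurrence by 4 weeks, or the 4-week phrase may attach to bleeding alone. What is supported is that the item is undefined.
- A reader might take 6.7–7.9% as the chance of a false success. Only about half of those rejections favour sarpogrelate.
- The late-rise rates have no source in the protocol. The assumption that they are equal across arms and unaffected by treatment is also untested, given 4 weeks of sarpogrelate.
- The Kaplan-Meier method is named only for plotting, and chi-square is named for categorical variables. A curve that is coarse after day 2 does not undermine the primary test.

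**Conclusion.** The point holds as an internal contradiction: the primary outcome window is wrong as written, and primary and secondary CIN are not distinguished. This rests on the text alone and needs no assumed rate. It must be corrected, because the trial is open-label and the window decides which patients count as events.

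The numerical consequences are illustrative. The inflation of type I error is moderate and arises only if significance on either window would be claimed. The loss of power arises only if the 4-week window is used and late rises unrelated to contrast occur at the assumed rates. The low starting power comes from the sample-size calculation and is not part of this point.

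A reader might also infer that the protocol settles on 48 hours. It does not. That window is recommended because it is the only one operationally defined, not because the document declares that it governs.

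**What to change.** Before any comparison of outcomes by arm, issue a dated amendment; one is needed because recruitment began in April 2010. It should:

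1. State one primary outcome, in the same words, in the Abstract, the primary hypothesis and Primary Outcome Measurement. CIN within 48 hours of contrast, compared as a proportion by chi-square, is the natural choice.
2. State that the 48-hour limit applies to both creatinine criteria.
3. Tie the 20% control rate in the Sample size section to that window.
4. Give the 4-week creatinine outcome its own name and definition as a secondary outcome.

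The Kaplan-Meier plot may stay as a descriptive display.

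The cost is wording plus the amendment process, with a record that the choice was made without sight of results by arm. No new samples or visits are needed, since every creatinine measurement is already scheduled. The registry entry was not available for this review and should be checked for the same conflict.
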